#### Statistical analysis

2.8.2

Stepped-wedge cluster trials present a number of challenges related to intra-cluster correlation, the correlation between data repeated over time, and the need to monitor underlying temporal trends.^[47]^ Accordingly, the analysis of the primary endpoint (AEs/1000 patient-days) and other event rate secondary endpoints (e.g., number of AEs/100 admissions, preventable AEs/1000 hospital days etc.) will be based on mixed-effects Poisson regression models, entering as fixed effects the control period and a time term to account for a potential underlying trend in AE rates over the study period, and a random effect accounting for the unit level. A potential interaction term between time and intervention will be tested to identify a possible learning curve.^[5]^ Pre-specified supportive analyses will be performed to take into account possible changes in specific confounding factors over time by further adjusting for the demographic and clinical characteristics of children, including a lower term – GA at birth <28 weeks; birth weight <1000 g; length of hospital stay.^[9,19,25]^ Treatment-effect heterogeneity across clusters and varying secular trends across clusters will also be investigated by introducing the intervention and time terms as random slopes, respectively.^[51]^

The analysis of binary secondary endpoints will be based on mixed-effects logistic regression models, following similar modelling principles such as those previously described for the primary endpoint.

The descriptive analysis results will be presented as number (%) for categorical data or mean (standard deviation) or median (interquartile range) for continuous variables, depending on the characteristics of the observed distributions. Univariate comparisons between periods will rely on Student's *t* test for paired series or Wilcoxon signed ranks for quantitative variables, depending on the application conditions.

All missing or invalid data will be systematically checked and searched for in patients’ medical records. For multivariate analysis of the primary endpoint adjusting for potentially missing confounders, in addition to complete case analysis, a sensitivity analysis will be led using multiple imputation by chained equations to check the robustness of the findings

All analyses will be performed with Stata v16.0 (StataCorp, College Station, TX, USA).

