## Introduction

1

Since 1999, medical errors (MEs) have been recognized as a leading source of mortality in patients.^[1]^ Recent reports suggest that as many as 250,000 to 400,000 patients die each year in the United States as a result of MEs and that millions of preventable injuries occur per year due to MEs.^[2]^ MEs have been defined as unintended acts in the process of care, either omission or commission, or acts that do not achieve their intended outcome.^[3,4]^ Most MEs do not result in harm to the patient, but a proportion of them causes harm^[5,6]^; these MEs are called preventable adverse events (AEs) – injuries or damages resulting from a medical intervention or omission of an intervention. Consequences of AEs vary in severity, from treatment modifications to contributing to death.^[2,5,7]^

Common risk factors for AEs are invasive procedures, long hospital stays^[8–11]^ and organizational factors such as professionals’ turnover, night/day shifts, and complex transmissions.^[12,13]^

Neonates hospitalized in neonatal intensive care units (NICUs) are at high risk of ME-related damage. In this population, rates of AEs vary by degree of prematurity: the risk of AEs is 57% for extremely low-gestational-age (GA) neonates born before 28 weeks’ GA (ELGANs) as compared with 3% for term newborns.^[9]^ Supplementary risk factors in the ELGAN subgroup are clinical fragility due to low weight, overall immaturity and inability to compensate for clinical alterations as well as complex care (catheters, tubes, artificial ventilation) and types of medications needed.^[9,14–21]^ In addition, neonatal-specific AEs described include identification errors among multiple-birth infants,^[22]^ breast milk errors,^[21]^ skin lesions due to immaturity^[9,15]^ and nasal injuries from non-invasive ventilation.^[23]^ Finally, hospital-acquired infections (HAIs), especially central-line-associated bloodstream infections (CLABSIs) are a leading cause of mortality and neurological morbidity in premature neonates^[23–25]^ which can be reduced by adherence to appropriate infection control measures.^[26,27]^

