#### Sample size and power calculation

2.8.1

The primary endpoint is the rate of AEs/1000 patient-days (hospitalization days). Analysis of available data from the literature as well as our own unpublished routine data allowed for anticipating an average basal value of 60 AEs/1000 patient-days in the absence of any intervention. The calculation of the required sample size was based on the Poisson distribution to compare control and intervention AE rates. To do so, calculations were performed according to Hemming and Girling,^[49]^ derived from the initial approach by Hussey and Hughes,^[50]^ to take into account the effect of the stepped wedge (or design effect) study specification on the sample size calculation.

Considering a total number of 12 units divided into 3 randomization clusters over 5 study periods, a 5% two-tailed alpha risk and an intraclass correlation coefficient ranging from 0.01 to 0.1, we will need to include 15 patients per unit per month (i.e., 15 × 4 = 60 patients per cluster per 4-month evaluation period), for a total of 15 × 20 × 12 = 3600 patients over the study period, a cumulative 61,200 to 72,000 patient-days corresponding to an expected mean hospitalization length from 17 to 20 days) to show, with a power of 80%, a minimum relative reduction of 17% in rates of AEs (i.e., a decrease from 60 [control] to 50 [intervention] AEs/1000 patient-days).

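### The primary Poisson model allows for differences between units but not between infants, so its standard error is probably too small and the planned power too high

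*Protocol article*

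**What the plan says.** Section 2.8.2 states that the primary endpoint and the other event-rate endpoints "will be based on mixed-effects Poisson regression models". The fixed effects are the study condition and time, "and a random effect accounting for the unit level". The section names no infant-level term, overdispersion parameter or robust variance. Gestational age below 28 weeks, birth weight below 1000 g and length of stay enter only in supportive analyses. The random slopes mentioned there vary across clusters.

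Section 2.8.1 makes the matching assumption: "The calculation of the required sample size was based on the Poisson distribution to compare control and intervention AE rates". It uses "a 5% two-tailed alpha risk and an intraclass correlation coefficient ranging from 0.01 to 0.1" and claims to detect, "with a power of 80%, a minimum relative reduction of 17% in rates of AEs", that is "a decrease from 60 [control] to 50 [intervention] AEs/1000 patient-days".

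On how far infants differ, the Introduction says "the risk of AEs is 57% for extremely low-gestational-age (GA) neonates born before 28 weeks", against 3% for term newborns.

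**The concern.** The endpoint counts every AE, and about one is expected per infant, so several AEs in one infant will be common. Once the unit effect is given, a Poisson model sets the variance of the count equal to its mean. A unit intercept takes up differences between units only. If infants within a unit and period differ in daily AE rate, the counts vary more than the model allows. Summing the counts to unit-period totals does not remove the excess.

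The primary test would then reject too often when the programme has no effect, and the confidence interval would be too narrow. The sample size makes the same assumption, so the stated power would be too high.

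**Working it through.** **Inputs from the protocol.** 12 units in 3 sequences; five 4-month periods; 60 charts per unit per period; 60 against 50 AEs/1000 patient-days; mean stay 17 to 20 days; two-sided 5%; intraclass correlation 0.01 to 0.1. Expected AEs per infant under control are 0.060 × 17 = 1.02 to 0.060 × 20 = 1.20. At the average of the two rates (0.055/day) they are 0.935 to 1.10.

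**The plan's own figure.** I used the Hussey–Hughes variance with a unit intercept, categorical period and Poisson within-unit variance, and counted all five periods and 3600 infants. Power is:

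| Mean stay | ICC 0.01 | ICC 0.1 |
|---|---|---|
| 17 days | 0.790 | 0.754 |
| 20 days | 0.851 | 0.819 |

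So the stated 80% is about what Poisson variance gives, with nothing added for differences between infants. (Counting all periods departs from the Figure 1 legend, which leaves the transition phase out of the primary analysis. That is a separate matter and plays no part below.)

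**Effect on the standard error.** Let theta be the variance of the infant-specific multiplier on the daily AE rate. The protocol does not give theta, so it is an assumption. With equal stays:

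- dispersion = 1 + theta × mean AEs per infant
- true SE / model SE = √dispersion
- actual two-sided error = 2 × [1 − Φ(1.96 / √dispersion)]

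| theta (assumed) | Dispersion, 17–20 days | SE ratio | Actual error at nominal 5% |
|---|---|---|---|
| 0 | 1.00 | 1.00 | 5% |
| 0.25 | 1.23–1.27 | 1.11–1.13 | 8% |
| 0.5 | 1.47–1.55 | 1.21–1.24 | 11–12% |
| 1 | 1.94–2.10 | 1.39–1.45 | 16–18% |
| 2 | 2.87–3.20 | 1.69–1.79 | 25–27% |

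**Simulation check.** The Figure 1 design was simulated 1500 times per setting with no intervention effect, a 17-day stay and gamma-distributed infant multipliers. The fitted model was Poisson with unit intercepts (fixed, standing in for the random intercept), categorical period and no infant term. Rejection was 4.3% at theta 0, 11.9% at 0.5, 17.9% at 1 and 26.4% at 2. So the model is calibrated when infants do not differ, and the formula is confirmed when they do. With stays of coefficient of variation 1 (a further assumption), rejection rose to 16.7%, 25.9% and 36.8% at theta 0.5, 1 and 2.

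**Could length of stay explain the 3% to 57% range?** Converted to cumulative hazards, −ln(1 − 0.57) = 0.844 and −ln(1 − 0.03) = 0.030, a ratio of about 28. If infants below 28 weeks stay five times as long (assumed), 28 / 5 leaves about a 5.5-fold difference in daily rate. Take only two risk groups with 20% high-risk, a mean stay of 18.5 days and 0.055 AEs/day overall. The dispersion is then 1.64 and the actual error 12.6%. Varying the high-risk share from 10% to 30% and the stay ratio from 3 to 8 gives 6% to 32%. This borrows only the ratio of the two risks, because the cited source may have ascertained AEs differently.

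**Power.** For a design that otherwise has 80%, power = Φ[(1.96 + 0.84) / √dispersion − 1.96]. Dispersion 1.5 gives Φ(0.33) = 63%; dispersion 2 gives Φ(0.02) = 51%.

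**Rare endpoints.** With 0.05 to 0.1 events per infant and theta 1 (both assumed), dispersion is 1.05 to 1.10 and the actual error 5.6% to 6.2%.

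**The case against.** The strongest reply is that the article condenses a fuller plan. It does not state the variance estimator or a fallback for overdispersion, and nothing in it rules out a robust variance. This stands as a limit on certainty: the consequence is likely, not established. It does not remove the point, because the article does fix the distribution and names "a random effect accounting for the unit level" as the only one in the main model, and its sample size uses Poisson variance.

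A reader might take the 3% and 57% as proof of a large spread in daily AE rate. They are risks per infant from a cited source, while the endpoint is per patient-day. An exposure offset absorbs whatever part of the gap comes from longer stay, and the protocol does not give stay by gestational age. The figures make equal daily rates implausible, but they do not measure theta.

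The protocol also deserves credit for its supportive adjustment for gestational age, birth weight and stay. That would remove part of the heterogeneity and show whether the conclusion is sensitive to it, but it does not protect the primary test. The cluster-level random slopes do not address differences between infants. Section 2.8.2 acknowledges correlation over time, but answers it with the time term and the unit effect.

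Infants contributing to both control and intervention periods could offset the effect. With a 4-month transition and a mean stay of 17 to 20 days, they will be few.

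**Conclusion.** The point holds for the primary endpoint. The stated model and sample size make no allowance for differences in daily AE rate between infants in the same unit and period, so the primary standard error is likely too small. It would be right only if all such infants shared one daily rate.

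The size depends on an assumed theta: an actual error of about 8% at 0.25, 11–12% at 0.5 and 16–18% at 1, with equal stays, and more if stays vary widely. Power of 80% would become about 63% at dispersion 1.5 and 51% at dispersion 2.

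Three stronger readings are not supported:

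- That the 5% level is known to be broken by a particular amount. The protocol gives no theta, and small values do little harm.
- That every rate endpoint is seriously affected. Dispersion grows with events per infant, so rare outcomes such as catheter-related bloodstream infection barely change.
- That this issue alone takes power far below 50%. Such figures come from also excluding the transition phase, or from a theta near 2.

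**What to change.** In section 2.8.2, specify the primary analysis at infant level with log patient-days as offset and a variance that allows for infant-level overdispersion. Any of these would serve:

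- a mixed negative binomial model;
- a Poisson model with an infant random intercept nested in unit;
- a cluster-robust variance with a small-sample correction for 12 units.

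Use the same approach for other frequent event-rate endpoints. In section 2.8.1, restate the power with an assumed dispersion factor and show a range.

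No new data are needed, because charts are already reviewed infant by infant. The cost is a change of wording, wider confidence intervals and a less favourable stated power.

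### The primary Poisson model has only a unit-level random effect, so block-to-block variation within units would make its standard error too small and its 5% test too liberal

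*Protocol article*

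**What the plan says.** Section 2.8.2 (Statistical analysis) names correlation between repeated measurements over time as one of the challenges of a stepped-wedge trial. It then fixes the primary model: mixed-effects Poisson regression, fixed effects for study condition and a time term, "and a random effect accounting for the unit level". That is the whole random part of the primary model.

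The same paragraph adds: "Treatment-effect heterogeneity across clusters and varying secular trends across clusters will also be investigated", by giving the intervention and time terms random slopes. It does not say that the primary test would change as a result.

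Section 2.8.1 (Sample size and power calculation) sets the design: "Considering a total number of 12 units divided into 3 randomization clusters over 5 study periods", with "a 5% two-tailed alpha risk and an intraclass correlation coefficient ranging from 0.01 to 0.1". It gives no cluster autocorrelation and no other measure of how a unit's rate varies between periods. The legend of Figure 1 excludes each unit's 4-month transition block from the primary endpoint analysis.

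**The concern.** A single random intercept assumes that each unit departs from the common time curve by a constant amount. Any two blocks of the same unit are then equally correlated, however far apart they are. The paragraph names correlation over time as a problem, but the model chosen in response allows only this simplest form of it.

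The article itself gives reasons to expect more. Its Introduction lists staff turnover among AE risk factors and reports an AE risk of 57% in infants born before 28 weeks against 3% at term, so a change in a unit's case mix would move its rate. Hospital-acquired infections, which can cluster in time, count among the AEs. A secondary outcome examines nurse and patient numbers as influences on AE rates.

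At stake is the false-positive rate of the primary test. If it is well above 5%, a programme without effect could be reported as reducing AEs.

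**Working it through.** **Inputs from the article.** 12 units in 3 sequences of 4, and 5 blocks of 4 months. 15 patients per unit per month, so 60 per unit-block. Mean stay 17 to 20 days. Control rate 60 per 1000 patient-days. ICC 0.01 to 0.1. Transition block excluded, which leaves 12 × 4 = 48 unit-blocks.

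**Assumptions, not in the documents.** The unit-by-block SD ω on the log rate, or equivalently the cluster autocorrelation (CAC). Between-unit log variance of 0.05 in step 2. Time entered as categorical blocks.

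**1. The plan's own figure.** The target is "a decrease from 60 [control] to 50 [intervention] AEs/1000 patient-days" with 80% power. I used generalised least squares under the Hussey–Hughes model (unit random intercept, period effects, Poisson patient variance, two-sided z test). With all 60 unit-blocks kept, power for ICC 0.01, 0.05 and 0.1 is 79.0%, 75.9% and 75.4% at a 17-day stay, and 85.1%, 82.4% and 81.9% at 20 days. This brackets the stated 80%, so the planning figure is consistent with a model that has no unit-by-period variance. It is reached only when the transition blocks are counted. Without them, power is 37% to 47%, which is a separate point.

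**2. Reported against true standard error.** Expected AEs per control unit-block are m = 60 × 17 × 60/1000 = 61.2. The working covariance is W = I/m + 0.05 × (same unit). The true covariance is T = W + ω²I. The reported variance is the intervention element of (X′W⁻¹X)⁻¹. The true variance is that of the same estimator under T. Type I error = 2[1 − Φ(1.96 × reported SE / true SE)].

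| ω | Reported SE | True SE | Type I, 17 days | Type I, 20 days |
|---|---|---|---|---|
| 0 | 0.105 | 0.105 | 5.0% | 5.0% |
| 0.05 | 0.105 | 0.113 | 6.7% | 7.1% |
| 0.10 | 0.105 | 0.133 | 12.1% | 13.3% |
| 0.15 | 0.105 | 0.161 | 20.0% | 22.2% |

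The SEs are for the 17-day stay. Hand check: the estimate is almost wholly within-unit, so the SE ratio is near √(1 + mω²). At ω = 0.10 this is √1.612 = 1.27, 1.96/1.27 = 1.54, and the two-sided p is about 12%.

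**3. Tied to the article's ICC range.** With 17 × 60/1000 = 1.02 expected AEs per patient, the total between-unit log variance is ICC/(1 − ICC)/1.02, that is 0.0099, 0.0516 and 0.1089 for ICC 0.01, 0.05 and 0.1. At an assumed CAC of 0.8, ω = √(0.2 × variance) = 0.045, 0.102 and 0.148. The SE pairs (reported/true) are 0.0998/0.1052, 0.1048/0.1330 and 0.1059/0.1609, giving 6.3%, 12.2% and 19.7%.

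**4. Simulation of the stated model.** Laplace maximum likelihood, z test, 2000 null trials per setting, 17-day stay:

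| CAC | ICC 0.01 | ICC 0.05 | ICC 0.1 |
|---|---|---|---|
| 1 | 6.2% | 4.7% | 5.3% |
| 0.95 | 6.8% | 7.0% | 8.9% |
| 0.9 | 6.3% | 8.3% | 12.5% |
| 0.8 | 6.8% | 13.3% | 21.2% |

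Monte Carlo SE is about 0.5 point near 5% and 0.9 point near 20%. With a linear time term at CAC 0.8 the figures are 6.9%, 13.9% and 21.1%, so the form of the time term matters little.

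**5. After the fix.** I analysed unit-block log rates with unit and period effects, the residual variance estimated across unit-blocks, and a t reference on 48 − 12 − 4 − 1 = 31 degrees of freedom. Over 20,000 trials per setting, type I error is 4.9% to 5.2% in every setting.

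**The case against.** The best defence has four parts.

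- **Heterogeneity is not ignored.** Random slopes for intervention and time are pre-specified, and that deserves credit. But they are not the primary test, and slopes do not absorb irregular block-to-block shifts. In a check at ω = 0.10, adding them left type I error at 11.5% to 12.5%.
- **The size depends on an unknown.** This stands. No unit-by-block SD or CAC is given. At ICC 0.01 an SD of 0.10 for block shifts alone would use up the whole between-unit variance (SD √0.0099 ≈ 0.10), and inflation there is only 6% to 7%.
- **A small-sample correction may be in the SAP.** A reader might infer that 12 units without a stated correction already break the 5% level. The documents do not support this. The article says nothing either way on the reference distribution, the SAP is not shown, and such detail is commonly left to it. Nor is it the driver: when the single intercept is correct, the uncorrected z test runs at 4.7% to 6.2%. Changing only to a t reference with 10 degrees of freedom still gives 8.9% and 15.2% at CAC 0.8 for ICC 0.05 and 0.1, and is conservative (2.6% to 2.8%) at CAC 1.
- **Larger figures overreach.** A reader might quote about 24% at ω = 0.15, or 18% at ω = 0.10 with patient frailty added. The first is high against the 20% to 22% calculated here. The second brings in overdispersion between patients, a separate assumption. Nor does the article say that the time term is linear.

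**Conclusion.** The point holds in a limited form. The primary model is stated with one unit-level random effect, it leaves unit-by-period variation out, and the additional slope analyses do not repair the primary test. If units' rates shift between blocks, the reported standard error is too small.

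Under assumed unit-by-block SDs of 0.05, 0.10 and 0.15, type I error is about 7%, 12–14% and 20–22%. At an assumed CAC of 0.8 it is about 6–7%, 12–13% and 20–21% for ICC 0.01, 0.05 and 0.1. Without such variation it is close to 5%. The documents do not show that the error rate is inflated in this trial. They show that the stated model gives no protection if the variation exists. The article's silence on a small-sample correction is not a fault in itself.

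**What to change.** Add a unit × period random intercept to the primary Poisson model, and name a reference distribution suited to 12 units. As an alternative, base the primary p-value on a randomisation test over the 12!/(4!)³ = 34,650 allocations of units to sequences. Either would do; both are not needed. The randomisation test needs the transition-block counts, because a re-allocated unit has a different transition block. The chart review samples all 20 months, so these counts will exist. Keep the random slopes for intervention and time as sensitivity analyses. Settle the choice before the outcome data are analysed.

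The cost is analysis-plan wording and computing time. The statistical price is wider intervals and lower power when the variation is present. With the transition blocks excluded and a 17-day stay, the analysis in step 5 has about 34% power for the planned effect at CAC 1, and 32%, 24% and 18% at CAC 0.8 for ICC 0.01, 0.05 and 0.1. Most of the gap to 80% comes from excluding the transition blocks, since the stated model itself has only 37% to 41% power in that setting.

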#### Other characteristics

2.7.4

Demographic data (birth date, sex, multiple gestation, etc.), medical data (gestational age at birth, birth weight, ventilation, central lines, etc.), and outcomes (mortality and specific outcomes) as well as ME and AE data (nature, severity of consequences, communication) and HAI data (dates, antibacterial treatment duration, data on blood cultures and local bacterial specimens) will be collected for all patients.

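### The primary Poisson model has no patient covariate; adjusting it for gestational age at birth would be a nearly free gain in precision and protection against chance case-mix imbalance.

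*Protocol article*

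**What the plan says.** Section 2.8.2 gives the primary model for AEs per 1000 patient-days as a mixed-effects Poisson regression. Its fixed effects are the control/intervention period and a time term; its random effect is the unit. No characteristic of the infant is included.

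Patient characteristics come in at the next level: "Pre-specified supportive analyses will be performed to take into account possible changes in specific confounding factors over time". The list given there is "GA at birth <28 weeks; birth weight <1000 g", plus length of hospital stay. It is introduced as an inclusion list, so it need not be complete.

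Two other places bear on this choice:

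- Section 2.7.4 (Other characteristics) lists among the data collected for all patients "medical data (gestational age at birth, birth weight, ventilation, central lines, etc".
- The Introduction states that "the risk of AEs is 57% for extremely low-gestational-age (GA) neonates born before 28" weeks, "as compared with 3% for term newborns".

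The chart-review sample is 15 files per unit per month drawn at random (sections 2.8.1 and 2.8.3), so 60 per unit per 4-month block. The legend of Figure 1 takes each unit's transition block out of the primary analysis.

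**The concern.** Control and intervention phases contain different infants, and each unit-block is a fresh random draw of about 60 charts. The share of very preterm infants therefore moves from block to block by chance. The unit random effect absorbs only stable differences between units. The time term absorbs only change shared by all units. What is specific to one unit in one block stays in the residual and feeds into the intervention contrast.

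With 12 units and 12 × 4 = 48 analysed blocks, this part averages out only partly. If AE rates per patient-day depend on GA, the primary rate ratio is less precise than the collected data allow, and one realisation may be pushed up or down by an imbalance that could have been adjusted for. GA at birth is fixed before admission, so the intervention cannot alter it and adjustment cannot remove any of the intervention effect.

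**Working it through.** **The plan's own figure.** Section 2.8.1 states 80% power for 60 versus 50 AEs per 1000 patient-days; no covariate enters that figure. I used the Hussey–Hughes variance with 12 units, 3 sequences and 5 blocks, block variance 0.055/(60 × stay), between-unit variance ICC/(1 − ICC) × 0.055, ICC 0.01–0.1 and two-sided 5%. With the transition block counted as intervention, power is 75% (17-day stay) to 82% (20-day stay) with categorical time, and 80% to 86% with linear time. The stated figure is reproduced on that basis. How the transition block is treated in the sample size is a separate matter, and nothing below depends on it.

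**The GA contrast.** 57% / 3% = 19. This is a ratio of risks per infant, whereas the endpoint is a rate per patient-day. Longer preterm stays are already in the denominator, so 19 cannot be used as a rate ratio.

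**Chance variation of case-mix.** Assumptions, none from the documents: a share p = 20% of charts below 28 weeks, stays k = 3–5 times longer, daily AE rate r = 2–3 times higher.

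- SD of the share in 60 charts: √(0.2 × 0.8 / 60) = 0.052, about 5 percentage points.
- Sensitivity of the block log rate to the share: d = (rk − 1)/(1 + (rk − 1)p) − (k − 1)/(1 + (k − 1)p). For r = 2, k = 3: 5/2.0 − 2/1.4 = 1.07. For r = 3, k = 3: 8/2.6 − 2/1.4 = 1.65.
- Added variance d² × p(1 − p)/60: 0.0031 and 0.0072.
- Poisson variance of the block log rate: 1/(0.055 × 60 × 18.5) = 0.0164.
- Added share: about 19% and 44% by this approximation. Exact binomial calculation over the four combinations of r and k gives 18–47%.

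For p = 10–30% and r = 1.5–3 the exact range is 4–91%. These are upper bounds, because all other variation is taken as pure Poisson. With gamma frailty of shape 2 between infants (also assumed), 18–47% falls to about 8–21%. Since 1 − √(1/1.08) = 4% and 1 − √(1/1.21) = 9%, the standard error (SE) then falls by roughly 4–9%.

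**Simulation of the adjusted model.** Patient-level Poisson regression with unit effects, time and a log patient-days offset; 300 replicates per scenario. Assumed: GA mean 32 weeks, SD 4; rate ratio for 26 versus 34 weeks of 1.5 to 3.3; gamma frailty of shape 2; unit-block case-mix SD of 0 or 0.5 weeks. Empirical SE of the log rate ratio, linear time:

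| Rate ratio 26 vs 34 weeks | Case-mix SD (weeks) | No GA | GA <28 weeks | Linear GA | Reduction, cut | Reduction, linear |
|---|---|---|---|---|---|---|
| 1.49 | 0 | 0.1456 | 0.1460 | 0.1453 | none | 0.2% |
| 1.49 | 0.5 | 0.1512 | 0.1505 | 0.1503 | 0.5% | 0.6% |
| 2.23 | 0 | 0.1499 | 0.1426 | 0.1424 | 4.9% | 5.0% |
| 2.23 | 0.5 | 0.1556 | 0.1387 | 0.1359 | 10.9% | 12.7% |
| 3.32 | 0 | 0.1765 | 0.1650 | 0.1582 | 6.5% | 10.4% |
| 3.32 | 0.5 | 0.1825 | 0.1669 | 0.1609 | 8.5% | 11.8% |

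Over all scenarios tried, linear GA cut the SE by about 0–20% and the 28-week indicator by about 0–16%, so the continuous term gained about 0–5 percentage points over the cut. Power rose by about 0–8 points. The mean estimate hardly moved: with rate ratio 2.23 and case-mix SD 0.5 it was −0.167 without GA and −0.168 with it. These runs used fixed unit effects and, in the tabulated set, a mean stay of about 14 days, so only the relative changes are informative.

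**The case against.** An unadjusted primary model with a pre-specified adjusted supportive analysis is a legitimate choice in a randomised trial, and the protocol shows that it had case-mix in mind. That stands: nothing here is wrong or contradictory. It also stands that the gain may be nil, since the inputs that decide its size are not in the documents.

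Four stronger readings are tempting, and the documents support none of them:

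- *The primary estimate is biased by case-mix drift.* Drift common to all units is taken up by the time term and stable unit differences by the unit effect. Section 2.8.2 also plans random slopes for time trends that differ between clusters. In simulation the mean estimate was almost unchanged by adjustment.
- *GA is the strongest predictor of AEs.* The Introduction gives a large contrast but no ranking. It also states "Common risk factors for AEs are invasive procedures, long hospital stays" and names organizational factors.
- *Cutting GA at 28 weeks is a serious loss.* The indicator recovers most of the gain in the scenarios above.
- *The point rests on a power shortfall.* It does not; it would apply at any power.

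A last objection is timing. Inclusion ended in November 2017 and chart review was to start in 2018, so changing the primary model late carries a pre-specification cost. That is a reason to fix and date the change before the outcome data are analysed and to keep reporting the unadjusted model; it does not defeat the change.

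**Conclusion.** The point holds as a recommendation on efficiency. GA at birth is collected for all patients, is related to AE risk on the protocol's own account and cannot be changed by the intervention, yet it is kept out of the primary model. Including it would remove a source of chance variation between unit-blocks that phase, time and unit terms leave in place. The expected benefit is an SE of the log rate ratio lower by about 0–20% and power higher by about 0–8 points. Both ranges depend on an assumed GA mix, assumed rate ratios per patient-day and assumed variation between infants. Moving GA into the primary model is the main action; using it as a continuous term is a minor refinement.

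**What to change.** Before the outcome data are analysed, amend section 2.8.2 so that the primary model is a patient-level mixed-effects Poisson regression with a log patient-days offset, phase, time, a unit random effect and GA at birth, preferably continuous. Because AEs are assigned to phase by date of occurrence, patient-days of a stay that crosses a phase boundary need to be split in the same way. Keep the model without GA as a named sensitivity analysis and report both. For any missing GA, the multiple imputation already planned for confounders can be used.

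The cost is a dated change of wording in the analysis plan. No new data are needed.
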